# Comparing the efficacy and safety of minimally invasive biportal endoscopic spine surgery versus conventional microscopic discectomy in single-level lumbar herniated intervertebral disc (ENDO-BH Trial): a multicenter, prospective, randomized controlled equivalence trial study protocol

**DOI:** 10.1186/s13063-022-06094-2

**Published:** 2022-02-22

**Keywords:** Lumbar disc herniation, Biportal endoscopic lumbar discectomy, Microscopic lumbar discectomy, Randomized controlled trial

## Abstract

**Background:**

Biportal endoscopic surgery has recently been performed in lumbar discectomy, with advantages over conventional surgery, such as less skin scarring and muscle damage. However, the clinical results have not been established. Although previous studies reported no difference between the biportal endoscopic and microscopic discectomy clinical results, the evidence was weak. Therefore, this study aims to evaluate the efficacy and safety of the biportal endoscopic discectomy versus the microscopic discectomy.

**Methods:**

This prospective multicenter randomized controlled equivalence trial is designed to compare the efficacy and safety outcomes of patients who underwent lumbar discectomy using biportal endoscopy or microscopy. We will include 100 participants (50 per group) with a lumbar herniated disc. The primary outcome will be the Oswestry Disability Index (ODI) score 12 months after surgery based on a modified intention-to-treat strategy. The secondary outcomes will include the visual analog scale score for low back and lower extremity radiating pain, the ODI score, the Euro-Qol-5-Dimensions score, surgery satisfaction, walking time, postoperative return to daily life period, postoperative surgical scar, and surgery-related variables, such as postoperative drainage, operation time, admission duration, postoperative creatine kinase, and implementation status of conversion to open surgery. Radiographic outcomes will also be analyzed using magnetic resonance imaging (MRI) or computed tomography (CT) and simple radiographs. Safety will be assessed by evaluating all adverse and severe adverse events and surgery-related effects. The participants will be assessed by a blinded assessor before surgery (baseline) and 2 weeks and 3, 6, and 12 months after surgery.

**Discussion:**

This trial will be the first prospective, multicenter, randomized controlled trial to analyze the efficacy and safety of biportal endoscopic discectomy in lumbar herniated disc.

This trial is designed for evaluating the equivalence of the results between biportal endoscopic and microscopic discectomy including adequate sample size, blinded analyses, and prospective registration to reduce bias. This trial will provide enough data on the effectiveness and safety of biportal endoscopic surgery and will be an important study that allows clear conclusions.

**Trial registration:**

Clinical Research Information Service (cris.nih.go.kr.) (KCT0006191). Registered on 27 March 2021

## Background

Discectomy for herniated discs is the most common method for resolving a patient’s symptoms [1, 2]. Currently, microscopic discectomy, a minimally invasive surgery, is performed to address the problems of conventional open discectomy [3]. As a representative method, microscopic discectomy, which uses a tubular retractor and an endoscope, is the most commonly used minimally invasive surgery method [1]. Minimally invasive surgery has many advantages over conventional methods, and reports indicate that the clinical results do not differ from conventional methods [3, 4]. A full-endoscopic discectomy (uniportal) is a minimally invasive surgery with a single very small incision. According to a randomized controlled trial by Gibson JNA et al., full-endoscopic discectomy showed similar functional improvement compared to microscopic discectomy, and it showed reduced length of hospital stay and less leg pain at 2 years after surgery [5]. However, the procedure is difficult to learn, has a narrow field of view and a long operation time, and may cause problems, such as insufficient discectomy [6].

Recently, the biportal endoscopic spine surgery was developed [7–13]. This surgical technique uses two small skin incisions, called portals, to access the surgical site, minimizing the damage to normal structures. Consequently, there are fewer post-surgical complications, such as postoperative pain and muscle damage. Additionally, arthroscopic instruments for knee and shoulder joint surgery can be used, eliminating the need to purchase additional equipment. Spinal instruments familiar to the spine surgeon, such as Kerrison punches and pituitary rongeurs, can also be used.

There are several retrospective clinical reports of biportal endoscopic discectomy [7, 14, 15]. A previous study reported that the clinical feasibility and results of biportal endoscopic discectomy were similar to conventional discectomy. However, the evidence suggesting advantages to biportal endoscopic discectomy was weak owing to the small number of patients, and the study was retrospective. Therefore, a randomized controlled trial (RCT) is warranted. This multicenter, prospective RCT will compare the outcomes of biportal endoscopic versus microscopic discectomy. We hypothesize that the efficacy and safety of biportal endoscopic discectomy and microscopic discectomy in the lumbar spine will be similar.

## Methods/design

### Trial design

The design and protocol of this multicenter, assessor-blind, prospective, parallel randomized controlled equivalence trial were approved by the institutional review board of participating hospitals in Korea. Participants will be randomly allocated 1:1 to either active intervention group or control intervention group. Participants randomized to active intervention group will undergo biportal endoscopic discectomy. And participants randomized to the control intervention group will undergo microscopic discectomy. Participants will visit the hospital for a minimum of 12 months at 2 weeks, 3 months, 6 months, and 12 months after surgery to evaluate the participant’s outcome.

### Participant population

One hundred adults aged 20–80 years with radiating pain in the lower extremities will be recruited across six hospitals. Enrollment eligibility will be determined based on the inclusion and exclusion criteria.

### Inclusion criteria

Aged 20–80 years oldLumbar herniated intervertebral disc disease at one levelRadiating pain to the lower extremities (visual analog scale [VAS] score > 4)Able to understand and consent to the researchWilling to participate and to comply with our proposed follow-up protocol

### Exclusion criteria

Spondylolisthesis (Meyer grade ≥ II)Spinal stenosis more than moderate degree (Schizas classification ≥ grade B) [16]A history of lumbar spinal surgery at the same levelDegenerative lumbar scoliosis (Cobb angle > 20°)Other spinal diseases (e.g., ankylosing spondylitis, spine tumor, fracture, or neurologic disorders)Psychological disorders (e.g., dementia, intellectual disability, or drug abuse)Other disorders which the surgeon considers inappropriate for participation

### Recruitment

Participants will be recruited from those who decided to perform a one-level discectomy for lumbar disc herniation in each hospital; subjects will not be recruited by social media. Potential participants will be screened by the researcher to determine participation eligibility, and eligible participants will undergo baseline testing with a blind assessor. All participants will receive a baseline test and outcome assessment after providing written consent to the researcher.

### Randomization and follow-ups

Participants will be randomized into either the control (microscopy) or intervention (biportal) group at a 1:1 ratio, following a computer-generated randomization list prepared by a researcher with block sizes of four. The randomization lists will be incorporated into a web-based eCRF platform (iCReaT; internet-based clinical research and trial, icreat.nih.go.kr) accessible to authorized researchers. The randomization process will be processed independently at each hospital and completed by the researchers. Allocation will be concealed in opaque envelopes numbered consecutively and presented to the surgeon immediately before surgery.

Participants will visit the hospital for a minimum of 12 months at 2 weeks, 3 months, 6 months, and 12 months after surgery to evaluate the participant’s outcome. The participant’s primary and secondary outcomes will be collected by an independent researcher during in-hospital visits but can be evaluated over the phone if unavoidable circumstances arise (Fig. 1).

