### Blinding

This is a single (assessor) blind trial comparing biportal endoscopic discectomy with standard treatment (microscopic discectomy); the participants and surgeons will know what surgery they have undergone. Therefore, only the assessor will be blinded, and the blinded outcome assessor will measure and collect all outcomes before and after surgery, with a single-blind in each hospital. Each assessor will attend a training session prior to data collection to ensure consistency across hospitals. The outcome assessor will provide a detailed justification if unblinding occurs.

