#### Statistical analysis

All statistical analyses will be conducted using Stata/MP 15.1 (StataCorp LLC, College Station, TX). A two-sided *P*-value < 0.05 will be considered statistically significant. The Shapiro-Wilk test will be used to evaluate the distribution of the collected data. Normally distributed continuous variables will be presented as the mean and standard deviation (SD), whereas non-normally distributed variables will be presented as the median and interquartile range. Categorical variables will be presented as numbers and percentages (%).

Both modified intention-to-treat (mITT) and per-protocol analyses will be performed. The mITT strategy will be the main analysis and indicates that participants are analyzed on whether they underwent a randomly assigned surgery (to avoid the effects of crossover and dropout, which may break the random assignment to the treatment groups). Excluded participants before and after surgery will be excluded from the analysis, and participants exceeding the calculated sample size will not be recruited.

The surgical intervention effect 12 months after surgery will be assessed by the ODI scores and a two-sided 95% confidence interval (CI) as the primary outcome and then compared between the groups. Biportal endoscopic discectomy will be considered equivalent to microscopic discectomy if the upper and lower limit of 95% CI of the ODI score at 12 months is limited to within the pre-defined equivalence limit of 12.8 points. To analyze the serial effect on secondary clinical outcomes (i.e., VAS pain scores for the back and lower extremities and the ODI, EQ-5D, and POSAS score), a linear repeated-measures mixed model will be used. Time will be analyzed as a categorical variable (2 weeks and 3, 6, and 12 months) and include the intervention-time interaction to analyze the effects of surgery during the follow-up periods. Inter-group differences during the 12-months will also be analyzed using a linear repeated-measures mixed model, controlling for baseline and follow-up time points as categorical variables. Other clinical, radiographic outcomes and adverse effects between two groups will be analyzed using Student’s *t*-test for continuous variables and the chi-square test for categorical variables.

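### One fixed block size of four, apparently run separately in each hospital with unblinded surgeons, makes up to a third of allocations certain for an observer who knows the earlier ones

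*Protocol article*

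**What the plan says.** Under Trial design, the ratio is fixed: "Participants will be randomly allocated 1:1 to either active intervention group or control intervention group". Under Randomization and follow-ups, assignment is made "following a computer-generated randomization list prepared by a researcher with block sizes of four". Four is the only size given, and no variation in size is described. The same section says: "The randomization process will be processed independently at each hospital and completed by the researchers". With the plural used for the lists, this reads as one sequence per hospital, although the word stratified does not appear.

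Two carriers of the allocation are named in that section. First: "The randomization lists will be incorporated into a web-based eCRF platform". Then: "Allocation will be concealed in opaque envelopes numbered consecutively and presented to the surgeon immediately before surgery". It does not say which of the two governs.

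Two other statements bear on the point. Under Blinding, "the participants and surgeons will know what surgery they have undergone". Under Exclusion criteria, the last item is open-ended: "Other disorders which the surgeon considers inappropriate for participation". The evaluation schedule (Table 1) places consent, eligibility and baseline ODI at the screening visit and randomization at the operation visit.

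**The concern.** Concealment has two parts. The next slip must be hidden, and it must not be deducible from the slips already opened. Opaque envelopes handle the first. A short block of one constant size weakens the second in an open-label surgical trial, because each operation reveals an allocation and the block must end two against two.

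Foreknowledge matters only if someone can act on it. Here they could, through whom they approach, when surgery is booked, or the judgement-based exclusion. Nor does the analysis set clearly protect against removal after allocation: "Excluded participants before and after surgery will be excluded from the analysis".

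If patients with a better outlook were steered towards one arm, the 12-month ODI difference would shift. In an equivalence trial such a shift could create a false difference or hide a true one. Participants are not blinded and the ODI is completed by the patient, so an unpredictable sequence is one of the main remaining protections.

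**Working it through.** The plan gives no figure on predictability, so there is none to reproduce.

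**Inputs.** Block size 4 and separate running at each hospital (Randomization and follow-ups); ratio 1:1 (Trial design); 100 participants in six hospitals (Participant population). Assumption: roughly equal recruitment, 100/6 = 16.7 per hospital, taken as four hospitals with 17 and two with 16.

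**Step 1: certain assignments in a complete block.** There are six orderings of two biportal and two microscopic slips. An assignment is certain once one arm is used up.
- Positions 1 and 2: never certain.
- Position 3: certain when the first two were the same arm, 2 of 6 orderings = 1/3.
- Position 4: always certain.

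Expected number per block = 1/3 + 1 = 4/3, so the share is (4/3)/4 = 33.3%. In general a block of size 2m gives 1/(m+1): 25% for size 6 and 20% for size 8.

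**Step 2: best guessing.** Guess the arm with more slips left, and toss a coin when level.
- Position 1: 1/2.
- Position 2: 2/3.
- Position 3: 1/3 × 1 + 2/3 × 1/2 = 2/3.
- Position 4: 1.

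The sum is 2.833, and 2.833/4 = 70.8%, against 50% by chance.

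**Step 3: the whole trial.** A hospital with 16 or 17 patients completes four blocks; a 17th patient opens a new block and is not predictable. Each hospital therefore has 4 × 4/3 = 5.33 certain assignments, and six hospitals have 32 of 100. Three less even splits (such as 30, 20, 20, 10, 10, 10) gave 30.7. For a 17-patient hospital the certain share is 5.33/17 = 31.4%, and best-guess success is (4 × 2.833 + 0.5)/17 = 69.6%.

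**Step 4: an observer who sees only some cases.** The number of surgeons per hospital is not stated. Suppose each earlier allocation is known independently with probability p, and the position in the block is known. Certainty then requires having seen both slips of the exhausted arm, which has probability p². The share in complete blocks becomes p²/3:
- p = 1: 33.3%
- p = 0.75: 18.8%
- p = 0.5: 8.3%

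**Step 5: randomly ordered sizes.** This was simulated with 17 patients per site and 10,000 runs. The observer knows all earlier allocations and the set of sizes, but not their order.

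| Block sizes | Certain in advance | Best guess correct |
|---|---|---|
| 4 only | 31.4% | 69.6% |
| 4, 6 | 5.9% | 67.8% |
| 4, 6, 8 | 2.3% | 66.5% |
| 2, 4, 6 | 3.7% | 68.9% |

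Varying the size removes most of the certainty but little of the guessing.

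**The case against.** The strongest objection is that the one-third figure describes an ideal observer. It needs knowledge of the block size, of the starting point and of every earlier allocation at the hospital. The documents do not say that any surgeon follows colleagues' cases. This stands, and Step 4 shows how quickly the figure falls.

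A reader might infer that publication revealed the block size throughout the trial. It did not: recruitment began in July 2021 and the article appeared in February 2022. Later recruitment, estimated to run to July 2023, is exposed. Whether surgeons knew the size before publication is not stated.

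A reader might also infer that enrolling staff can look up the next assignment in the eCRF, or that the person who prepared the list also screens patients. Neither is shown. The phrase about authorized researchers can describe the platform rather than the list, and researcher is a generic word. A condensed article may leave access rights and separation of roles to the full protocol. The list and the envelopes may also be successive steps of one process, so this is an ambiguity and not a breach.

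Existing safeguards count too. Table 1 puts consent, eligibility and baseline ODI before randomization, and the envelope reaches the surgeon only just before surgery. This narrows the scope for steering after screening. It does not prevent a deduction from past allocations before a patient is approached.

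Finally, no effect on the ODI has been estimated, and the documents give no basis for one. Adjustment for baseline ODI could address measured imbalance, but not unmeasured prognosis.

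**Conclusion.** The concern holds as a predictability risk in a stated design rule. It is exact for a fully informed observer: 33.3% of assignments certain and 70.8% guessed correctly in complete blocks. Across the trial this is about 31 to 32 certain assignments of 100. These totals rest on separate sequences per hospital (the natural reading), on an assumed split of patients across sites, and on full knowledge of earlier allocations. For less informed observers the share is smaller, by an amount the documents do not determine.

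The documents do not support saying that concealment was broken, that anyone could view the list, or that the ODI comparison is biased. The two carriers of the allocation need one clarifying sentence. The point merits correction because the remedy is cheap.

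**What to change.** For allocations not yet issued, regenerate each hospital's list with randomly ordered block sizes, for example 4 and 6, or 4, 6 and 8, and do not disclose sizes or order to the sites. State one governing release mechanism, preferably web release patient by patient once eligibility and baseline are recorded. If envelopes are kept, say that they only convey that result.

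The cost is new lists and a minor amendment. The statistical downside is a slightly larger possible imbalance within a hospital: an unfinished last block can leave the arms apart by at most 2 with size 4, by 3 with size 6 and by 4 with size 8. Because best-guess success hardly changes, the single controlled release matters as much as the new sizes. If all allocations have already been issued, the lists cannot be changed; the trial report should then state the block size, who knew it and which mechanism governed.

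### Randomisation is blocked within each of six hospitals, but no described analysis includes hospital; if outcomes differ between hospitals, the confidence intervals are somewhat wider than necessary

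*Protocol article*

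**What the plan says.** **Allocation.** Under Randomization and follow-ups, patients are allocated 1:1, "following a computer-generated randomization list prepared by a researcher with block sizes of four", and "The randomization process will be processed independently at each hospital and completed by the researchers". Participant population says that the 100 adults "will be recruited across six hospitals". The word stratified does not appear, but the section speaks of lists in the plural, and blocks run independently at each hospital amount to stratification by hospital.

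**Analysis.** The Statistical analysis section describes three kinds of comparison:

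- Primary: a 95% interval for the 12-month ODI, compared between groups. Equivalence is concluded "if the upper and lower limit of 95% CI of the ODI score at 12 months is limited to within the pre-defined equivalence limit", which is set at 12.8 points. No test, model or covariate is named.
- Serial outcomes: linear repeated-measures mixed models with time and the intervention-by-time interaction, and for the overall group difference "controlling for baseline and follow-up time points as categorical variables".
- Other clinical and radiographic outcomes and adverse effects: these "will be analyzed using Student’s *t*-test for continuous variables and the chi-square test for categorical variables".

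Hospital appears in none of the three.

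**The concern.** Blocking within hospital balances the arms at each site, so differences between hospitals largely cancel out of the treatment comparison. An analysis without hospital does not use this. It leaves the between-hospital variation in the residual, so the reported standard error is larger than the true sampling error of the difference.

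In an equivalence trial the conclusion depends on the whole interval fitting inside the margin, so unnecessary width reduces the chance of a positive conclusion. The same mechanism applies to operation time, admission duration and drainage. These plausibly depend on local practice, and the article assigns them unadjusted t-tests.

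**Working it through.** **Inputs from the article.** SD of 12-month ODI 17.1, margin 12.8, follow-up loss 20%, 50 per group (Sample size); 95% interval rule (Statistical analysis); six hospitals (Participant population); blocks of four (Randomization and follow-ups).

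**Assumed input.** The share ρ of 12-month ODI variance that lies between hospitals is not given. I use 0, 2%, 5% and 10%, and take 17.1 as the total SD.

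**Step 1: the plan's own figure.** Two one-sided tests at 0.05 each, true difference 0, power 0.90: n = 2 × (17.1 × (1.645 + 1.645) / 12.8)² = 38.6, so 39 per group, or 40 with the t distribution. Then 40 / 0.80 = 50, which reproduces the stated size. That calculation corresponds to a 90% interval. Under the stated 95% interval, 40 evaluable per group gives about 82% power. This mismatch is a separate matter; here it only sets the starting point.

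**Step 2: interval half-width at 40 evaluable per group.**

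- Without hospital: t(78) × 17.1 × √(2/40) = 1.991 × 3.824 = 7.61.
- With hospital as five fixed-effect terms: t(73) × 17.1 × √(1 − ρ) × √(2/40) = 1.993 × 3.824 × √(1 − ρ).

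**Step 3: power at true difference 0.**

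- Without hospital, the reported half-width stays near 7.61, but the true standard error of the difference is 3.824 × √(1 − ρ), because blocking has removed the hospital component. Power ≈ 2Φ((12.8 − 7.61) / (3.824 × √(1 − ρ))) − 1. At ρ = 10%: 5.19 / 3.628 = 1.43, giving 84.7%.
- With hospital: t-based power of the two one-sided tests at 0.025 each, with residual SD 17.1 × √(1 − ρ) and 73 degrees of freedom.

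| Assumed ρ | Half-width without | Half-width with | Excess width | Power without | Power with | Gain in simulation (points) |
|---|---|---|---|---|---|---|
| 0 | 7.61 | 7.62 | −0.1% | 82.5% | 82.1% | −0.3 |
| 2% | 7.61 | 7.54 | 0.9% | 82.9% | 83.1% | 0 to 0.4 |
| 5% | 7.61 | 7.43 | 2.5% | 83.6% | 84.7% | 1.0 to 1.4 |
| 10% | 7.61 | 7.23 | 5.3% | 84.7% | 87.2% | 2.1 to 2.6 |

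The last column is the range over simulations with six sites, blocks of four and 80 evaluable patients. For ρ = 0 it comes from runs with equal and unequal site sizes. In ODI points the excess half-width is 0.07, 0.18 and 0.38 at 2%, 5% and 10%.

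**Step 4: direction of the error.** In simulation, the interval without hospital covered the true difference about 95.6% of the time at ρ = 5% and 10%. With the true difference placed at the margin, equivalence was declared in 2.4% and 2.1% of runs, against a nominal 2.5%. The error is conservative.

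**The case against.** The strongest reply is that only a condensed article is at hand. It leaves the primary model open and does not say that hospital will be ignored, and a centre term is the kind of detail a statistical analysis plan supplies. This stands for the primary outcome: a reader might infer that the article fixes an unadjusted primary analysis, and it does not. It stands less well for the rest. The mixed-model covariates are listed and the t-tests and chi-square tests are named, so adding hospital there would change stated methods.

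The reply is also right about size. Three stronger readings are tempting, and the documents do not support them:

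- *The primary interval is too wide, without qualification.* This requires 12-month ODI to vary between hospitals, and no figure for that is given. At zero variation nothing is lost.
- *Adjustment lifts power from a fixed 82% to about 83%, 85% and 87%, a gain of about 1, 3 and 5 points.* Blocking within hospital also raises the power of the unadjusted analysis, so the true gain is about half of that or less. Larger gains obtained by also adjusting for baseline ODI come mainly from the baseline correlation, not from hospital.
- *Site-driven secondary outcomes lose much more.* This is plausible, but the documents give no figures from which to compute it.

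Finally, separate lists per hospital is the natural reading of the randomisation text, not an explicit statement.

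**Conclusion.** The point holds as a modest and conditional gain in efficiency. The described analyses do not reflect the way patients are randomised. If 2% to 10% of 12-month ODI variance lies between hospitals, leaving hospital out makes the primary interval about 1% to 5% too wide, at most about 0.4 ODI points against a margin of 12.8, and costs between nearly nothing and about 2.5 points of power. These figures rest on the assumed shares, on 17.1 as the total SD, on 40 evaluable patients per group, on a true difference of zero and on separate blocked lists per hospital. The treatment estimate is not biased and the risk of a false claim of equivalence is not raised. The reason to act is that the change costs almost nothing.

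**What to change.** - State that randomisation is stratified by hospital, if that is what is done.
- Specify the primary analysis as a linear model for 12-month ODI with treatment and hospital (six levels), and take the 95% interval for the treatment difference from it. The estimate stays a mean difference in ODI points, so the 12.8 margin applies unchanged.
- Add hospital to the mixed models alongside baseline, time and the interaction.
- Replace the unadjusted t-tests for operation time, admission duration and drainage with linear models that include hospital.

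The cost is 5 degrees of freedom and some wording in the analysis plan. If hospitals turn out not to differ, the half-width goes from 7.61 to 7.62. Recruitment, data collection and sample size are unaffected.
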